#### Phase 2: Intervention

A total of 120 eligible participants were randomized to receive either 4000 IU (100 mcg) of vitamin D3-fortified fruit juice or placebo-fruit juice. Depending on the assigned group, the participants will be instructed to consume either vitamin D3-fortified fruit juice or placebo-fruit juice daily in the morning by diluting the powder in 150 ml of water for eight weeks. Additionally, participants will be reminded to maintain their dietary habits and physical activity, besides abstaining from donating blood during the study, which may interfere with the interpretation of study findings.

#### Clinic follow-up visits

Participants will be required to attend three clinic visits after fasting overnight (± 8 hours) throughout the study at the Department of Nutrition’s clinical laboratory, UPM, where the initial screening session will be carried out. Participants were only allowed to consume only water during the overnight fast. Each session will span approximately 30 minutes, between 8–10 am. The details of each clinic sessions are as follows **(Fig 2)**:

Clinic 1 (Week 0, baseline): Participants’ height (cm) will be measured by using a digital stadiometer and weight (kg) using weighing scales, followed by the collection of a 10 ml fasting venous blood sample. Then, they will be given a 3-day food diary to be completed at home before the clinic meeting and collected during the clinic session. An 8-week supply supplement container containing fruit juice powder in sachets with assigned participant ID will be provided to them. At the same time, the participants will be briefed on the protocol, and an email will be sent one day prior to the following clinic appointment as a reminder.

Clinic 2 (Week 4, interim): The same procedure will be repeated except for height measurement. Participants will be given a 3-day food diary to be completed before the next clinic.

Clinic 3 (Week 8, post-intervention): The same procedure will be repeated except for height measurement. Later, the final 3-day food diary and supplement container (with any) of the remaining fruit juice powder in sachets will be collected to calculate the adherence.

**Fig 2 pone.0265772.g002:**
[figure not shown]
Study protocol overview.

#### Venepuncture procedure and blood sampling

Venepuncture will be performed by a trained phlebotomist (supervised by a medical doctor who is a research team member) to obtain 10 ml of venous blood samples from participants at each clinic session. Both whole blood and plasma obtained from the venepuncture will be utilized in the study analysis. Blood samples were collected in lithium heparin and EDTA blood collection tubes (BD Company, New Jersey, USA) for the various blood biomarker analysis. Whole blood samples will be analyzed immediately after collection to measure full blood counts (FBC). On the other hand, venous blood samples will be centrifuged for 10 minutes (1600 g) at 4°C to obtain plasma samples required for iron and vitamin D biomarkers detection, which will then be aliquot into microcentrifuge tubes and stored at -80°C before analysis. Besides, plasma samples collected at three time-points (baseline, interim and post-intervention) will be used to analyze iron status biomarkers (C-reactive protein, ferritin and hepcidin) and vitamin D metabolism biomarkers (25-OH D) concentrations using commercially available ELISA assay kits specific to different biomarkers.

### Study outcomes and measures

#### Primary outcomes

Blood samples will be collected at three time points during the 8-week course of the study to determine iron status changes and vitamin D biomarkers. The study’s primary outcome will be ferritin concentration, which has been demonstrated to be well-associated with iron storage in the absence of inflammation [27]. A higher concentration of ferritin may be observed with inflammation despite low iron stores, causing the interpretation to be more complex [27]. Nonetheless, this situation can be controlled by measuring the c-reactive protein (CRP), which is included as part of the biochemical analyses in this study. Meanwhile, the full blood count indices (FBC) will provide the amount of functional iron utilized to produce red blood cells [28]. Besides, a peptide hormone that functions to downregulate iron absorption known as hepcidin [29] is also measured to investigate its mechanistic role in iron metabolism homeostasis following vitamin D administration. Plasma 25(OH)D concentration will be measured to determine the circulating vitamin D.

FBC profiling will be carried out using an automated Beckman Coulter Ac.T diff Hematology Analyzer (Bechman Coulter Inc California, USA) and compared to the normal values/ranges [30]. Reagents used to include Coulter reagents and Coulter rinse shutdown diluent will be obtained from Beckman Coulter Inc, California, USA. Besides, commercially available ELISA assay kits will be utilized to determine the iron and vitamin D biomarkers status by measuring the plasma C-reactive protein (CRP) (R&D Systems Inc, Minneapolis, USA), ferritin (Elabscience Biotechnology Co. Ltd), and hepcidin (R&D Systems Inc, Minneapolis, USA) concentrations for iron biomarkers status. Meanwhile, 25(OH)D (Calbiotech Inc, California, USA) concentration will be determined for vitamin D biomarker status. Readings from the concentrations will be compared to the normal thresholds of the specified blood biomarkers [24, 27, 31, 32]. Each ELISA kit assay will be purchased with quality controls (low, medium, high), including with expected range from similar companies supplying the specified kits. A similar assay for each biomarker will be used for all blood samples collected to account for inter-assay coefficient variations.

#### Other measures

Participants’ height will be measured to the nearest 0.1 cm with a wall-mounted digital stadiometer (Model 264 SECA, Hamburg, Germany), whereas their body weight will be recorded to the nearest 0.1 kg using an electronic scale (Model 875 SECA, Hamburg, Germany). The measurements will be obtained in compliance with the standardized methods and protocols by the International Society for the Advancement of Kinanthropometry (ISAK) in duplicates, while the instruments used will be calibrated to ensure accuracy. After that, the body mass index (BMI) will be calculated using the participants’ height and weight and compared to the cut-off point set by the World Health Organisation [33].

Participants will be required to complete a 3-day food diary at baseline and post-intervention (to include 2 weekdays and 1 weekend day) to estimate their habitual dietary intake. The diary comprised of instructions on how to record participants’ dietary intakes properly, including a guide to portion sizes, how to describe the foods/drinks in detail, together with a sample diary. In each section of the diary, columns for the time of consumption, location, description of food/drink consumed, brand and amount/quantity, physical activity, and recipe sections will be provided for the participants to complete. On top of that, they will be given another diary to complete and returned to the baseline and post-intervention clinic. Upon completion, their dietary records will be analyzed for nutritional content by using Nutritionist Pro Software (Axxya System LLC, Washington, USA), and the food items used for the analysis will be based on the Malaysian Food Composition Table [34]. The Malaysian Recommended Nutrient Intake (RNI) 2017 will be used as a reference to compare the participants’ energy, macro, and micronutrients intake [35].

A set of questions will be used to account for sun exposure which may confound study findings. Participants will be asked about their weekly duration under direct sunlight (minutes/day) to quantify sun exposure. Then, the scores will be calculated by multiplying the total daily exposure by the number of days in a specified week. Other than that, participants were required to detail their clothing style for sun protection level, including an umbrella, hat/cap, skin protection lotion, clothes such as long sleeves/pants or skirts and veils. In the end, the sun protection level will be determined by computing the total usage of the eight specified items with a max score of 8 (min = 0) [36]. Questions will be administered before the baseline clinic and during post-intervention clinic sessions.

### Data analysis

All statistical analyses will be performed using IBM SPSS Statistic Data Editor Software (Version 21). Kolmogorov-Smirnov tests and histogram will be used to determine the normality of the data, while the descriptive statistics will be used to describe the frequencies and median (range) or mean (standard deviation) for categorical and continuous data, respectively. Meanwhile, baseline and clinical characteristic comparisons between the groups (vitamin D and placebo groups) will be carried out using independent t-test or Mann-Whitney test for continuous data, and Pearson Chi-square or Fisher’s exact test for categorical data. Mean change from baseline to all follow time points of the primary outcomes (plasma ferritin, full blood counts, C-reactive protein, hepcidin and 25(OH)D) will be compared between treatment groups using repeated-measures analysis of variance (ANOVA). Additionally, treatment group, baseline characteristics, sun exposure and dietary intake will be used as fixed factor or covariates in the analysis. The adjusted mean difference with 95% confidence interval and Cohen d will represent the magnitude of the vitamin D effect. A 5% level of significance will be used to determine statistical significance in all analyses. Finally, treatment effects will be assessed using an intention-to-treat strategy. After that, the sensitivity analysis will be conducted with the last observation carried forward assumption for missing data for the primary outcome.

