### Power and sample size estimation

The sample size was estimated by using (mean ± S.D) serum ferritin concentrations (ug/dl) from a randomized trial carried out by Blanco-Rojo, Pérez-Granados [7] in 41 women aged 18–35 years with low iron stores to determine the effect of iron-fortified fruit juice consumption on iron and vitamin D status. At week 8, it was observed that (mean ± S.D) serum ferritin concentrations were significantly higher in the vitamin D group (34.1 ± 14.8 ug/l), compared to 24.8 ± 17.7 ug/l in the placebo group (p < 0.05). In this study, the effect size is calculated by dividing the mean difference (9.3 ng/ml) with the pooled standard deviation (16.29). With an effect size of 0.571, the total sample size will be required in the present study is 50 individuals/group (Power = 0.80, α err prob = 0.05). By considering a 20% drop-out rate, the total sample size required to demonstrate a significant difference in serum ferritin concentrations between the vitamin D group and placebo is estimated to be 120 (60 participants/group). The sample size was estimated using G-Power Software (Version 3.1.7).

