#### Phase 1: Recruitment and screening

The prevalence of iron deficiency based on plasma ferritin concentration (< 15 μg/l) in women aged 18–40 years in Malaysia was reported to be approximately 33% [25]. Meanwhile, the prevalence of adult women who consumed vitamin and mineral supplements based on the Malaysian Nutrition Adult Survey (MANS) 2014 was reported to be approximately 32.1% [26]. Considering these data, approximately 736 women would have to be screened to achieve the required sample size. All participants will be provided with a participant information sheet (PIS) and a date for the venous blood collection to ascertain their plasma ferritin and hemoglobin concentrations, to determine their iron stores and hemoglobin levels. Then, they will be provided with a written consent form and will be required to complete a screening questionnaire to ensure the eligibility criteria are met. The screening questionnaire will be used to obtain the participants’ socio-demographic characteristics, including age, ethnicity, religion, educational level, and household income.

During the screening session, 1 ml of venous blood will be collected at the clinical laboratory at the Department of Nutrition, UPM by a trained phlebotomist. The whole blood and plasma sample collected will be used to determine the concentrations of ferritin and hemoglobin. Once the blood analysis results are obtained, participants will be notified via email or phone. Eligible participants with marginally low iron stores and non-anemic will be invited to participate in Phase 2 of the study. On the other hand, those with abnormally high plasma ferritin concentrations (> 150 ug/l) and low hemoglobin concentrations (< 12 g/dl) from the screening will be advised to arrange a check-up with their registered general practitioner and excluded from the study.

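### Baseline significance tests between randomised arms tell the trial nothing, and the open covariate classes should give way to a short fixed list that always includes the week-0 value of the outcome

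*Protocol article*

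**What the plan says.** Two statements in the Data analysis section of the protocol article matter here.

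- Baseline tests: "baseline and clinical characteristic comparisons between the groups (vitamin D and placebo groups) will be carried out using independent t-test or Mann-Whitney test". Categorical variables get chi-square or Fisher's exact tests. The section Randomization and blinding of participants forms the same two groups by permuted blocks, 1:1.
- Outcome model: "treatment group, baseline characteristics, sun exposure and dietary intake will be used as fixed factor or covariates in the analysis". The model is a repeated-measures ANOVA of change from baseline.

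The article does not itemise these classes. Elsewhere it lists what is collected: "socio-demographic characteristics, including age, ethnicity, religion, educational level, and household income" (Phase 1: Recruitment and screening), BMI and "energy, macro, and micronutrients intake" (Other measures), and two sun scores, one for exposure and one for protection. The week-0 value of the outcome is not named as a covariate. The Power and sample size estimation section rests on a plain two-group comparison with no covariates.

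**The concern.** Under valid randomisation any baseline difference between the arms is due to chance. A test of that difference cannot inform the analysis, and a p-value below 0.05 invites a false claim of imbalance.

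The covariate sentence commits to classes, not variables. Several of the collected items have multiple categories, and nutrient intake alone could supply many terms, so the primary ferritin model could be anything from compact to very large for a trial of this size. The one covariate with an obvious claim to a place, week-0 ferritin, is not named. At stake are some precision in the primary comparison and the analyst's freedom to settle the model after seeing the data.

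**Working it through.** **Inputs from Power and sample size estimation.** Mean difference 9.3, pooled SD 16.29, "Power = 0.80, α err prob = 0.05", 120 women randomised. "By considering a 20% drop-out rate" gives 120 × 0.8 = 96 completers; the article does not state 96 itself.

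**Reproducing the plan's figure.** d = 9.3 / 16.29 = 0.571. For 50 per group, the noncentrality is 0.571 × √(100/4) = 2.855. A two-sided t-test at 5% then has power 0.807, which agrees with 50 per group. Sidedness is not stated; a one-sided test would need only 39 per group, so two-sided is the reading that fits.

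**Effect of covariates.** For N women, k covariate degrees of freedom (df) and joint R² with the outcome:

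- variance factor V = (1 − R²) × (1 + k/(N − 3 − k))
- noncentrality = d × √(N/4) / √V, with N − 2 − k error df

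This uses the same single-time-point comparison as the plan's sample size, not the full repeated-measures model. The documents give no R², so a range is shown.

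Unadjusted, N = 96: noncentrality 0.571 × √24 = 2.797, 94 df, power 0.791.

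Example, k = 20 and R² = 0: V = 1 + 20/73 = 1.274, noncentrality 2.797/√1.274 = 2.478, 74 df, power 0.687.

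| k (N = 96) | R² = 0 | R² = 0.10 | R² = 0.25 | R² = 0.50 |
|---|---|---|---|---|
| 1 | 0.786 | 0.827 | 0.889 | 0.973 |
| 3 | 0.777 | 0.819 | 0.882 | 0.971 |
| 5 | 0.768 | 0.810 | 0.875 | 0.968 |
| 10 | 0.743 | 0.786 | 0.855 | 0.959 |
| 20 | 0.687 | 0.732 | 0.806 | 0.933 |
| 30 | 0.621 | 0.667 | 0.745 | 0.894 |

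- **Break-even with no adjustment.** At 20 df and R² = 0.22, V = 0.78 × 1.274 = 0.994 and power is again 0.791. The break-even R² is about 0.11 for 10 df.
- **All 120 analysed.** Unadjusted power is 0.873. With 20 df and R² = 0, V = 1 + 20/97 = 1.206 and power is 0.805: lower, but still at the planned level.
- **Against a short model, same R² of 0.25.** 0.889 − 0.806 = 0.083 for one covariate, and 0.882 − 0.806 = 0.076 for three. Both are about 8 points.
- **If the other covariates add something.** In a simulation of 10,000 trials (N = 96), one covariate had R² 0.25 and 19 others added 0.10 jointly. The 20-df model had power 0.862 and the single-covariate model 0.888, a gap of under 3 points.

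**Baseline tests.** Assuming 20 independent tests at 5%, the expected number of false imbalances is 20 × 0.05 = 1, and the chance of at least one is 1 − 0.95^20 = 0.64.

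**If tests were used to select covariates.** The article does not say this; it is checked only as a risk. Simulation (N = 96, 20 candidates, 10,000 trials per scenario):

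| R² of the one prognostic candidate | Power, unadjusted | Power, selected by test | Type I error, selected |
|---|---|---|---|
| 0 | 0.789 | 0.767 | 0.049 |
| 0.25 | 0.787 | 0.775 | 0.044 |
| 0.50 | 0.788 | 0.784 | 0.035 |

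With R² 0.25, always adjusting for the prognostic covariate gives 0.890, about 11 points more than selection.

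**The case against.** A reader might infer three stronger things. The documents do not support them.

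1. *That 20 or more df will be spent on 96 women.* The article gives no count. Religion and income are only screening-questionnaire items, and nutrients are described as compared with recommended intakes. Between about 5 and 30 df fit the text, and 5 uninformative df cost only about 2 points. The analysis is by intention to treat on 120 randomised women, so 96 is an assumption. It is a reasonable one for week 8, because last observation carried forward is reserved for a sensitivity analysis.
2. *That chance imbalance chooses the model.* The tests and the covariates are described in separate sentences with no rule joining them. Selection is a risk the wording leaves open, not a stated plan.
3. *That adjustment costs power either way.* It does not in general. Twenty df gain power over no adjustment once joint R² passes about 0.22. Selection by test loses only about 0.4 to 2 points against the unadjusted analysis, and its type I error falls below 5%, not above.

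It is also fair to say that an itemised covariate list may sit in a full protocol or analysis plan that is not shown, that the phrase baseline characteristics could include week-0 ferritin, and that analysing change already uses the week-0 value. The last point helps less than it seems. Subtraction forces a slope of 1, whereas a covariate lets the data set it. With equal SDs and R² 0.25 (correlation 0.5), the change score has variance 2(1 − 0.5) = 1 times that of the week-8 value, so nothing is gained.

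Finally, baseline p-values do not in themselves alter the treatment estimate. All this stands, and it limits the point to what the article states and how it could be better fixed.

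**Conclusion.** The concern holds in a limited form. The baseline significance tests are stated in the article, are uninformative under randomisation, and should go; on its own that is a minor matter. The covariate sentence is the more useful target, because it commits to open classes and leaves the week-0 outcome unnamed.

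The worst case is a loss of about 10 points (0.79 to 0.69), and it needs 96 completers, 20 df and covariates unrelated to ferritin. The comparison that bears on action is with a short model of equal prognostic value: about 8 points at an assumed R² of 0.25, and less if the extra covariates carry information of their own. Entry at ferritin below 20 μg/l narrows the baseline range, so the R² of week-0 ferritin may be smaller than 0.25. At R² 0.10, one covariate gives 0.827 against 0.791 unadjusted, still a gain.

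The trial's validity is not in question. This is a gain in precision, and in protection from discretionary modelling, from data already collected.

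**What to change.** - In the primary ferritin model, replace the open classes with a short list fixed before unblinding that always includes week-0 ferritin. Choose any other members for their expected correlation with the outcome, never by baseline p-values.
- Do the same for each other outcome, with its own week-0 value in its own model. Baseline sun exposure may stay in the 25(OH)D model, where it is a plausible predictor; it need not be barred from every analysis.
- Present the baseline table by arm with descriptive statistics only, and delete the between-arm tests.

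The cost is wording in the Data analysis section and a baseline table without p-values. No new data, visits or participants are needed.

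### Data analysis labels five entries primary outcomes at 5%, while the outcome definition and the sample size make ferritin the only one

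*Protocol article*

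**What the plan says.** The protocol article describes the primary outcome in four places.

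- **Primary outcomes.** The heading is plural, but the text names one: the "primary outcome will be ferritin concentration". CRP is there to help interpret ferritin when inflammation is present, the blood count to show functional iron, hepcidin to study mechanism, and 25(OH)D to measure circulating vitamin D.
- **Power and sample size estimation.** The calculation gives the "total sample size required to demonstrate a significant difference in serum ferritin concentrations between the vitamin D group and placebo", using week 8 ferritin values from a published trial. No other outcome is sized.
- **Data analysis, main comparison.** "Mean change from baseline to all follow time points of the primary outcomes (plasma ferritin, full blood counts, C-reactive protein, hepcidin and 25(OH)D" is to be compared between groups by repeated-measures ANOVA. The same section adds: "A 5% level of significance will be used to determine statistical significance in all analyses".
- **Data analysis, sensitivity analysis.** The section ends in the singular, with a "last observation carried forward assumption for missing data for the primary outcome", and does not say which outcome is meant.

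No blood biomarker is called secondary anywhere. The only other category, Other measures, holds anthropometry, diet and sun exposure.

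**The concern.** The primary outcome determines what a trial may conclude. Here one section gives a single primary outcome and another gives five entries, one of which (full blood counts) is itself a set of indices. Both are current text.

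Two separate things are at stake. First, 25(OH)D reflects the supplement itself. If it carries the label primary, a significant primary result can be reported although iron stores have not moved. Second, if the remaining entries are each tested at 5% and each counts as primary, the chance of at least one false positive among them exceeds 5%. In either case a reader of the results could not tell whether the outcome put forward as primary was the prespecified one.

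**Working it through.** **1. The statements side by side.** Ferritin is the only outcome common to all the places that name a primary outcome, and the only one used for sizing. The plural list in Data analysis is the exception. It also sits badly with the supporting, mechanistic and exposure roles that Primary outcomes gives to CRP, hepcidin and 25(OH)D.

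**2. The plan's own figure.** Inputs from Power and sample size estimation: the effect size comes from "dividing the mean difference (9.3 ng/ml) with the pooled standard deviation (16.29"; power 0.80; alpha 0.05.

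- d = 9.3 / 16.29 = 0.571.
- Normal approximation, two-sided: n = 2 × (1.960 + 0.842)² / 0.571² = 48.1, so 49 per group.
- Two-sided t-test: 49.13, rounded up to 50 per group, as stated. Power with 50 per group is 0.807.
- A one-sided test would need only 38 to 39 per group, so the stated figure is a two-sided one.

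The stated 50 per group is therefore reproduced for ferritin as one outcome with the full 5%.

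**3. 25(OH)D.** The Introduction expects it to be higher in the vitamin D group. The article gives no effect size. Assuming a standardized difference of 0.8 to 1.0, a two-sided t-test with 50 per group has power 0.977 to 0.999. A significant result on this entry is then nearly assured, whatever happens to ferritin.

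**4. False positives among the other four entries.** Because a real difference in 25(OH)D is expected, it does not belong in a count of false positives. That leaves ferritin, full blood counts (counted as one test), CRP and hepcidin, each at 5%, all assumed truly null.

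- Independent tests: 1 − 0.95⁴ = 1 − 0.8145 = 0.185.
- Equally correlated normal test statistics, simulated with 400,000 draws and two-sided 5% limits: 0.174 at correlation 0.3, 0.157 at 0.5 and 0.129 at 0.7.

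The article gives no correlations, so these are assumed values. It does not say how many blood count indices will be tested; more than one raises the figures.

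**5. Could all five stay primary?** With Bonferroni at 0.05 / 5 = 0.01 each, and the blood count as one test, the same t-test calculation gives 73.3, so 74 per group before dropout. With 50 per group, power for ferritin falls from 0.81 to 0.59. The planned size supports one primary outcome, not five.

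**The case against.** The strongest reply is that the plural list is a slip of labelling and not a plan for five co-primary outcomes. The outcome definition, the sample size and the closing singular all fit ferritin, and the roles of the other markers are already described. That is a plausible reading, and it makes the correction easy. It does not remove the conflict, because the list stands in the section that governs the analysis.

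Several stronger readings are tempting, and the article does not support them.

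- A reader might infer that any one significant biomarker makes the trial positive. Nothing in the article says so; it states no success rule at all. The harm lies in what the wording permits.
- A reader might quote 1 − 0.95⁵ = 22.6% for five tests. That counts 25(OH)D as a true null although a difference is expected.
- A reader might count 4, 8 or 11 blood count indices, add the other four entries and reach 34%, 46% or 54%. Neither the number of indices nor their independence is given, and indices from one blood count are linked.
- A reader might double the count for weeks 4 and 8. The plan is a repeated-measures ANOVA for each outcome, and no separate test at each week is stated.
- A reader might fault the absence of a multiplicity method for secondary outcomes. That is commonly left to an analysis plan, which is not shown here.

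**Conclusion.** The point holds as a contradiction within the article: five entries are called primary in Data analysis, against ferritin alone in the outcome definition and in the sample size. The text as written is wrong and leaves open which result decides the trial. This conclusion needs no assumption.

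The sizes attached to it do. The 18.5% falls to about 13% at a correlation of 0.7, and both figures treat the blood count as one test and all four entries as null. The near-certain 25(OH)D result rests on an assumed standardized difference of 0.8 or more. The documents do not support the claim that the trial is planned to be declared positive on any single marker.

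**What to change.** In Data analysis, replace the plural list with one primary outcome: plasma ferritin at week 8 (the time point used for sizing), vitamin D versus placebo, two-sided 5%. Relabel hepcidin and the full blood count indices as secondary, CRP as a supporting measure for reading ferritin, and 25(OH)D as a check of exposure. This matches the roles already given under Primary outcomes. State that the conclusion on iron stores rests on ferritin, and name ferritin in the sensitivity analysis sentence. How the secondary p-values are handled can be left to the analysis plan.

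The change is wording only. The calculated 50 per group and its power of 0.81 are unaffected. The price is that results on hepcidin, the blood count, CRP and 25(OH)D can no longer be presented as confirmatory.

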**Methods:**

In a placebo-controlled, double-blind, RCT, a total of 120 women aged between 19–40 with serum ferritin < 20 μg/l and fulfilled the eligibility criteria will be randomized into consuming either vitamin D3-fortified fruit juices containing 4000 IU (100 mcg) (vitamin D) or placebo-fruit juices (placebo) daily for eight weeks. At every 4-week interval, 10 ml fasting blood sample, information on dietary habit and anthropometric measurement will be collected. A mixed model repeated-measures analysis of variance will be performed to determine the effect of the intervention and the interaction with time points for all iron and vitamin D status blood biomarkers.

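### The sample size is for a week-8 ferritin difference, but no stated analysis makes that contrast the primary test, so the 80% power does not attach to the planned test

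*Protocol article*

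**What the plan says.** **Endpoint.** Under Primary outcomes: "The study’s primary outcome will be ferritin concentration". That sentence gives no time point.

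**Power.** Power and sample size estimation takes week-8 values from an earlier fruit-juice trial: "serum ferritin concentrations were significantly higher in the vitamin D group (34.1 ± 14.8 ug/l". The figure given there for the other arm is 24.8 µg/l with SD 17.7. The effect size comes from "dividing the mean difference (9.3 ng/ml) with the pooled standard deviation (16.29", and "With an effect size of 0.571, the total sample size will be required in the present study is 50 individuals/group". Both the difference and the SD are of ferritin levels at one visit. No SD of change and no correlation between visits enters. A 20% drop-out allowance brings the total to 120.

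**Analysis.** Data analysis takes the mean change from baseline to every follow-up visit, which "will be compared between treatment groups using repeated-measures analysis of variance (ANOVA". It then lists baseline characteristics, sun exposure and diet as possible factors or covariates, without naming baseline ferritin, and promises an adjusted mean difference. The abstract's Methods paragraph describes a mixed-model repeated-measures ANOVA "to determine the effect of the intervention and the interaction with time points for all iron and vitamin D status blood biomarkers".

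**The concern.** A repeated-measures ANOVA over several visits produces more than one test of treatment, and none of its standard overall tests is a week-8 comparison. If the outcomes are the changes at weeks 4 and 8, the group effect averages the two visits, and the group-by-time term asks only whether the effect at week 8 differs from that at week 4. If the outcomes are the values at weeks 0, 4 and 8, the group effect also averages in a visit at which the arms should not differ.

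Two things are at stake. The 80% figure describes a test that the protocol does not say it will run. And because no single effect or contrast is designated, the deciding test could be picked after the results are known.

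**Working it through.** **1. Reproduce the stated figure.** d = 9.3 / 16.29 = 0.571. The equal-weight pooled SD is √[(14.8² + 17.7²)/2] = 16.31, close to the stated 16.29. A two-sample t-test at two-sided 5% has noncentrality d / √(2/n). With n = 50 this is 2.85 and power is 80.7%, so 50 per group is reproduced as a plain t-test on week-8 levels. With 20% loss from 60, n = 48, noncentrality is 2.80 and power is 79.1%.

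**2. Power of the tests a reader could take from the text.** The document gives no visit correlations, no baseline or week-4 SD and no week-4 effect. Assumptions: 48 per arm, the same SD at all three visits, one common correlation r, and half the week-8 effect at week 4. In SD units the effects at weeks 0, 4 and 8 are 0, 0.2855 and 0.571. For each single contrast, noncentrality = effect / √(2 × variance / 48).

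| Test | Effect | Variance | Power at r = 0.3 / 0.5 / 0.7 |
|---|---|---|---|
| Group effect, average of week-4 and week-8 change | 0.428 | 1.5(1 − r) | 53 / 67 / 87% |
| Interaction, week 4 versus week 8 | 0.2855 | 2(1 − r) | 22 / 28 / 43% |
| Group effect over weeks 0, 4 and 8 | 0.2855 | (1 + 2r)/3 | 47 / 40 / 34% |
| Interaction over weeks 0, 4 and 8 (2 df) | – | – | 54 / 70 / 90% |
| Week-8 change alone | 0.571 | 2(1 − r) | 65 / 79 / 95% |
| Week 8 adjusted for baseline ferritin | 0.571 | 1 − r² | 83 / 89 / 97% |

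Worked line at r = 0.5: averaged change 0.428 / √(2 × 0.75 / 48) = 2.42, or 67%; baseline-adjusted week 8, 0.571 / √(2 × 0.75 / 48) = 3.23, or 89%. At r = 0.2 the adjusted week-8 contrast has 81%.

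**3. Vary the week-4 effect.** If the full effect is present at week 4, the averaged change has 77 / 89 / 99% at r = 0.3 / 0.5 / 0.7, and the week-4-versus-8 interaction falls to 5%, the significance level. The adjusted week-8 contrast is unchanged, since it does not use the week-4 effect.

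**4. Vary the baseline SD.** Entry requires ferritin below 20 µg/l, so baseline SD is probably well below 16.29; values spread evenly from 0 to 20 would have SD 20/√12 = 5.8. Take 5 (assumed), with week-8 SD 16.29.

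- Week-8 change has variance 25 + 265.4 − 2r × 5 × 16.29, that is 257.8 at r = 0.2 and 208.9 at r = 0.5. Power is 80% and 88%, so using change in place of level costs almost nothing here.
- With half the effect at week 4, week-4 SD 16.29, baseline correlation 0.2–0.5 and week-4-to-8 correlation 0.5–0.7, the averaged change has 63–81%, the three-visit group effect 54–62% and the week-4-versus-8 interaction 28–43%.
- The adjusted week-8 contrast has 81–89%.

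The loss is driven mainly by averaging in other visits or testing the interaction.

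**The case against.** Several points on the other side have force.

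- **The power loss rests on assumptions.** This stands. With a high correlation or an effect complete by week 4, the averaged change is above 80%. A reader might infer that the trial is underpowered, or that its deciding test must be weaker than the one planned. The documents do not support that, because they give none of the inputs that would settle it.
- **Comparing change at all follow-up visits could include a week-8 comparison.** It could, and that reading has adequate power over much of the range. But the text does not select it as primary.
- **Change scores need not be unadjusted.** A reader might infer that the plan throws away precision by ignoring baseline. The list of covariates may cover baseline ferritin, and if so the change model gives the same treatment estimate as an adjusted analysis of level. With the small baseline SD that the entry limit suggests, the penalty is in any case slight. What remains is that baseline ferritin is not named.
- **The abstract and Data analysis need not conflict.** A group effect and a time interaction are ordinary outputs of a repeated-measures ANOVA, and an abstract condenses. The problem is that no output is chosen.
- **Scale.** A reader might take 24.8 ± 17.7 as proof that ferritin must be log-transformed. That is one arm of a 41-woman source trial, and the other arm (34.1 ± 14.8) does not point the same way. The protocol plans normality checks, and transformation can be left to the analysis plan.
- **The analysis plan is not shown.** It may fix the primary contrast. But the protocol itself states both a power calculation and an analysis, and as written the two do not match.

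**Conclusion.** The point holds in a limited form. The powered comparison is a week-8 difference in ferritin level. The stated analysis is a repeated-measures ANOVA of change at all follow-up visits, described in the abstract as an intervention effect and a time interaction. No test is designated as primary, so the 80% cannot be read across.

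Depending on which output decides the trial, power at 48 per arm could be as low as about 22–53% at correlation 0.3 with half the effect at week 4, or above 80% under more favourable inputs. These are illustrations under assumed correlations, SDs and week-4 effect, not a forecast. That the planned and powered tests differ does not depend on them. The 50 per group is adequate, on the protocol's own effect and SD, for a week-8 contrast adjusted for baseline. This should be corrected, but it does not call the design into question.

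**What to change.** In Data analysis, name one primary test: the vitamin D minus placebo difference in plasma ferritin at week 8, adjusted for baseline ferritin, estimated from the repeated-measures model with a treatment-by-visit term and reported with its 95% confidence interval. List baseline ferritin explicitly among the covariates. Make the week-4 contrast and the group-by-time test secondary. Give week 8 as the time point under Primary outcomes, and bring the abstract's sentence into line.

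The cost is wording only, with no extra participants, visits or samples. There is one small downside: if the full effect is already present by week 4, a baseline-adjusted average over weeks 4 and 8 would have more power. Under equal SDs at r = 0.3 its variance is (1 + r)/2 − r² = 0.56 and its power is about 96%, against 83% for week 8 alone. With half the effect at week 4 the order reverses, about 79% against 83%. Week 8 is the visit the sample size was built on, and its power does not depend on the unknown week-4 effect.
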